**Weight gain**

Weight gain speed will be calculated as follows: [weight gain rate (g/kg /day)] = [1000 × ln(discharge weight/birth weight)]/(age at discharge  − age at return to birth weight).

**Length of hospital stay**

The length of hospital stay will be determined by recording the admission and discharge dates for each infant, allowing for calculation of the total duration of hospitalization.

**Height and head circumference**

Height and head circumference will be recorded both at admission and discharge.

**Follow-up**

The feeding performance, height, weight, head circumference will be evaluated at the corrected ages of 6 and 12 months and neurodevelopmental outcomes will be evaluated at the corrected ages of 18 to 22 months.

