## Objectives {7}

(i)Feeding outcomes: To determine the influence of differing initiation times of OMIs on feeding outcomes among preterm infants.(ii)Long-term growth and development: To examine the effects of OMIs with varying initiation times on extended growth and development trajectory of preterm infants.(iii)Neurodevelopmental outcomes: To explore the effects of OMIs with different initiation times on neurodevelopmental outcomes in preterm infants.

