**Table 2 Tab2:**
[figure not shown]
Study timeline

t1 started to feed; t2 after 48 h of discontinuing non-invasive ventilation; t3 full oral feeding; t4 discharge; t5 follow-up at 6 months after discharge; t6 follow-up at 12 months after discharge; t7 at the corrected age of 18–22 months

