### Data management {19}

Establishment of the data monitoring committee to strictly control the data collection. Demographic and background clinical data describing the sample that will be collected from the electronic medical record system will include maternal parity, maternal age, maternal disease, pregnancy complications and co-morbidities, conception method, delivery method, infant GA at birth, infant birth weight, infant height, infant head circumference, infant Apgar scores, infant sex, diagnoses, and so on.

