## Statistical methods

### Statistical methods for primary and secondary outcomes {20a}

The intention-to-treat analysis (ITT) will be the main analysis, with a per-protocol set (PPs) analysis conducted simultaneously. A significance level of *P* < 0.05 will be considered statistically significant. In the ITT analysis, all subjects will be included in the group to which they are assigned, regardless of whether they completely received the intervention. (1) Descriptive statistics will be used to summarize baseline characteristics. Continuous variables will be presented as Mean ± Standard deviation and categorical variables as percentages (%). (2) For comparisons between groups, Student *t*-tests will be applied for continuous variables, and chi-square tests will be utilized for categorical variables. (3) Assessment of efficacy: for continuous variables, independent Student *t*-tests will be employed for evaluation if conditions are met. (4) For data that do not follow a normal distribution, ordinal data, or data with significantly unequal variances, non-parametric tests will be used. The statistical analysis will be conducted using the medical statistical software SPSS 23.0 (SPSS, IBM Corporation, Armonk, NY, USA).

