### Methods for additional analyses (e.g., subgroup analyses) {20b}

The sub-group analysis based on gestational age will be performed. If required, according to the type of variable and their distributions, linear or logistic regressions will be performed. Multivariate regressions will also be conducted for selected outcomes, if necessary. In cases where a baseline characteristic in the enrolled population differs between the two groups with a *P* < 0.05 in the univariate analysis, then the results will be adjusted for that variable).

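### Growth at 6 and 12 months defaults to an unadjusted test, and covariate adjustment depends on chance baseline imbalance, so the long-term growth objective loses precision that collected data could recover

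*Protocol article*

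**What the plan says.** Objective (ii) of the protocol article is "To examine the effects of OMIs with varying initiation times on extended growth and development trajectory of preterm infants". The Follow-up paragraph under Outcomes {12} supplies the measurements: "The feeding performance, height, weight, head circumference will be evaluated at the corrected ages of 6 and 12 months". It names no analysis scale: no z-score, centile or change from birth. The legend to Table 2 times the same visits differently: "t5 follow-up at 6 months after discharge; t6 follow-up at 12 months after discharge".

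Statistical methods {20a} gives the tests. For comparisons between groups, "Student *t*-tests will be applied for continuous variables, and chi-square tests will be utilized for categorical variables". For efficacy, independent t-tests "will be employed for evaluation if conditions are met". The fallback is: "For data that do not follow a normal distribution, ordinal data, or data with significantly unequal variances, non-parametric tests will be used". None of these carries covariates.

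Additional analyses {20b} plans a subgroup analysis by gestational age. It says that, if required, "linear or logistic regressions will be performed", with multivariable models for selected outcomes where necessary. Its one firm rule on adjustment is that a baseline variable enters when a univariate test shows the arms to differ on it at P < 0.05.

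Data management {19} lists the baseline items, including "infant GA at birth, infant birth weight, infant height, infant head circumference, infant Apgar scores, infant sex". The secondary-outcome paragraph on height and head circumference has both measured at admission and at discharge.

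**The concern.** Size in later infancy can be expected to vary with sex and with size at birth. The trial enrols infants of 29+0 to 34+6 weeks under 2500 g, and the section on sequence generation describes no stratification. An unadjusted test leaves all of this variation in the error term.

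The adjustment rule does not repair that. Under randomisation, any one baseline variable differs at P < 0.05 about 5% of the time, so about 95% of the time a given covariate would not be brought in by the rule, however strongly it predicts the outcome. The gain from adjustment comes from prognostic strength, and a baseline significance test does not measure prognostic strength.

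What is at stake is the width of the intervals for one of three stated objectives. The sample size rests on transition time alone, so growth has no power claim behind it. Loss to follow-up by 6 and 12 months would widen those intervals further.

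**Working it through.** **The plan's own figure.** The article gives no sample size or precision for growth. Its 126 per group (140 after dropout) is for transition time, and I use it below only as a reference size. With a difference of 13.40 − 11.36 = 2.04 days, SD 4.99 and two-sided 5%, 126 per group corresponds to 90% power; the stated 80% would need 94. That is a separate matter and does not affect the growth point.

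**What the covariates might explain (assumptions, not in the document).**
- Sex, half boys, gap of d within-sex SDs: R² = (d²/4)/(1 + d²/4). For d = 0.4 this is 0.04/1.04 = 0.04; for d = 0.7 it is 0.1225/1.1225 = 0.11.
- Birth size correlated 0.3 to 0.5 with later size: R² = 0.09 to 0.25.
- With no overlap the sums would be about 0.13 to 0.36. I use a combined range of 0.10 to 0.30.

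**Formulas.** Residual SD = SD × √(1 − R²). Equivalent n = n/(1 − R²). Detectable difference at 80% power in SD units = √(2/n) × (1.960 + 0.842) × √(1 − R²).

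**Results at 126 analysed per group.**

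| R² | Residual SD | Equivalent n | Detectable difference (SD) | Power for 0.353 SD |
|---|---|---|---|---|
| 0 | 1.000 | 126 | 0.353 | 80% |
| 0.10 | 0.949 | 140 | 0.335 | 84% |
| 0.20 | 0.894 | 157.5 | 0.316 | 88% |
| 0.30 | 0.837 | 180 | 0.295 | 92% |

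The relative gain, 1/(1 − R²) − 1, does not depend on n: 1/0.9 gives 11% and 1/0.7 gives 43%. Confidence intervals narrow by 1 − √(1 − R²), about 5% to 16%.

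**With fewer infants followed.** The article gives no expected loss by 6 or 12 months. If 98 of 140 per group were seen (30% lost, an assumption), the unadjusted detectable difference would be 0.400 SD. Adjustment would bring it to 0.380 (R² 0.10) or 0.335 (R² 0.30).

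**Visit timing.** If visits fall at a corrected age, infants are measured at about the same corrected age. If they fall a fixed time after discharge, two infants discharged at different postmenstrual ages differ in corrected age at the visit by that same gap. This adds age variation to any unstandardised measurement. The two statements cannot both describe the schedule.

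**The case against.** The strongest reply is that this asks a condensed article for detail that belongs in an analysis plan not shown here. The scale and covariates of a secondary follow-up outcome are ordinary content for such a plan. The methods section is a general list that never mentions growth, and {20b} leaves regression open.

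Much of that stands, and it rules out several stronger readings:
- A reader might infer that growth will be compared as raw values. The article does not say so. It is silent on scale, and a z-score could be set elsewhere.
- A reader might infer that adjustment is excluded. It is conditional.
- A reader might count the whole gestational-age range as noise. Visits at corrected age already remove part of that component.
- A reader might infer that everything needed for z-scores is already recorded. The article does not list the exact age or date at the follow-up visit. It gives height and head circumference at admission and does not label them as birth values.
- A reader might take 140 to 180 per arm as the sample forgone. The 126 beneath it is the primary-outcome size, not a number promised at 6 or 12 months.

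The reply does not dispose of the adjustment rule. That rule is a positive statement about how covariates enter, and it is a poor one. An analysis plan faithful to the article would carry it forward.

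**Conclusion.** The point holds as a minor one about precision. As written, the default for height, weight and head circumference at 6 and 12 months is an unadjusted test, and adjustment is triggered by chance imbalance. Prognostic variables already collected would usually be left out.

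Randomisation keeps the unadjusted comparison unbiased, apart from whatever loss to follow-up introduces, and these are secondary outcomes. The document does not support a claim of bias or of an invalid growth analysis.

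The size of the loss is unknown. An effective sample size 11% to 43% larger rests wholly on an assumed R² of 0.10 to 0.30. The direction does not: any R² appreciably above zero means avoidable variance.

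The conflict over visit timing between the Follow-up paragraph and the Table 2 legend is in the text itself and needs resolving in any case.

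**What to change.** For the 6- and 12-month growth outcomes, replace the P < 0.05 trigger with a model fixed in advance and used whatever the baseline balance. Either form would do:

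1. A linear model for each measure with arm, sex, gestational age and the birth or admission value of the same measure.
2. Sex-specific z-scores at the exact corrected age on the visit date, against a named growth reference, in a linear model with arm, the baseline z-score of the same measure and gestational age.

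Report the adjusted difference with its confidence interval as the main growth result and show unadjusted values descriptively. Reconcile the Follow-up paragraph with the Table 2 legend on visit timing, and record the date of each visit so that exact corrected age can be computed.

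The cost is a change of analysis wording before unblinding, plus a recorded visit date and a chosen growth reference if z-scores are used. No further infants or measurements are needed.

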**Safety indicators**

Safety indicators in this study encompass the rate of adverse events occurring during the intervention period. Adverse events are defined as incidents related to this study that are unplanned, unexpected, or typically undesirable such as emesis, aspiration, oxygen desaturation, bradycardia, and other non-routine nursing incidents that may compromise child safety or elicit nursing complaints. Additionally, these incidents may also encompass asphyxiation, tachycardia, tachypnea, bradypnea, apnea, and oral infections.

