### Eligibility criteria {10}

Inclusion criteriaDiagnosis as preterm, with a birth weight of less than 2500 g, and gestational age ranging from 29^+0^ to 34^+6^ weeks.Stability of vital signs.Absence of major congenital anomalies, such as congenital heart disease, or congenital digestive tract malformations.Requirement non-invasive ventilation support, including the use of a high-flow nasal cannula.Enrollment within the first 72 h of life.

Exclusion criteriaRequirement of mechanical ventilation.Severe asphyxia.Prior enrollment in other studies.Diagnosis of necrotizing enterocolitis (NEC).Diagnosis of periventricular leukomalacia (PVL).Diagnosis of intracranial hemorrhage grade III or higher.Need for reinitiation of non-invasive ventilation support after the start of the OMIs.

There are termination criteria and they are as follows: (1) Occurrence of severe adverse events and complications during the trial. (2) Withdrawal of consent by the parents of the subject. Patients who enter the trial but fail to complete it due to any reason will be considered dropout cases. This includes cases where the doctor determines that the subject has withdrawn from the trial, as well as cases where the subject withdraws on their own, regardless of the timing or reason for withdrawal. All data on the infants will still be recorded.

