##### Early OMIs group

On the basis of routine care, we will implement an oral motor intervention program developed by American researcher Fucile, adapted for the Chinese context made by the domestic expert, Lv et al. [7, 15]. The program includes oral stimulation, which involves stimulation of the lips, cheeks, gums, and tongue, along with non-nutritive sucking. The intervention will start once the infant begins to receive milk and exhibits stable vital signs. It will be conducted once a day, for 15 min at a time, and will continue until the infant reaches full oral feeding and maintains it for 48 h without the need for tube feeding. The timing of each intervention is set for 15–30 min before any feeding session, within the hour of 8:00–18:00. All interventions will be performed by charge nurses who have received uniform training. If the infant experiences changes in their condition such as decreased oxygen saturation, bradycardia, or asphyxia, the intervention will be stopped.

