##### Late OMIs group

The interventions for OMIs will be initiated 48 h following the discontinuation of nasal continuous positive airway pressure. The early OMIs group and the late OMIs are the same in every aspect, with the sole distinction being the difference in the start time.

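### Adverse events are counted only during each arm's own intervention period, so events between the early and the late start of OMIs can count only in the early arm

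*Protocol article*

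**What the plan says.** The Safety indicators section sets the counting window: "Safety indicators in this study encompass the rate of adverse events occurring during the intervention period". It then sets what counts: "Adverse events are defined as incidents related to this study that are unplanned, unexpected, or typically undesirable such as emesis, aspiration, oxygen desaturation, bradycardia". The same section adds apnea, tachypnea, bradypnea, tachycardia, asphyxiation and oral infection. It gives no denominator for the rate.

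The window opens at a different point in each arm:

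- Early OMIs group: "The intervention will start once the infant begins to receive milk and exhibits stable vital signs".
- Late OMIs group: "The interventions for OMIs will be initiated 48 h following the discontinuation of nasal continuous positive airway pressure".

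It closes by one rule. The programme "will continue until the infant reaches full oral feeding and maintains it for 48 h without the need for tube feeding", and the Late OMIs group section describes the arms as alike, "with the sole distinction being the difference in the start time".

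Every infant is on respiratory support at entry. Inclusion criteria {10} list "Requirement non-invasive ventilation support, including the use of a high-flow nasal cannula". The footnote to Table 2 places the start of feeding (t1) ahead of 48 h off non-invasive ventilation (t2).

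The adverse event section {22} says that study-associated events will be documented and that infants are monitored during the intervention. It sets no window common to both arms.

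**The concern.** The start of OMIs is the randomised factor, and it also decides which days are open to adverse event counting. In the interval from first milk to 48 h after nasal CPAP ends, an early-arm infant is inside the counting window and a late-arm infant is outside it. Most of the listed events can occur in preterm infants without any OMI, and this is the interval in which the infants are youngest and on or just off support.

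Two things follow. Background events in that interval can add to the early arm's count and have no counterpart in the late arm. And if early OMIs prevented events there, the benefit would be invisible, because the late arm's events in the same interval are not counted.

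There is also friction with the ITT principle in section {20a}. A late-arm infant who leaves before OMIs begin has no intervention period and can contribute no event, yet stays in the ITT denominator.

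At stake is what the trial can say about the safety of starting earlier. Section {21b} plans no interim safety analysis, so the final comparison carries that evidence.

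**Working it through.** The protocol gives no adverse event figure to reproduce. The check has two parts: the length of the two windows, and what unequal windows do to a comparison when OMIs have no effect on events.

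**Inputs from the protocol**
- Pilot mean transition times: 11.36 days early, 13.40 days late (Sample size {14}).
- 48 h of maintained full oral feeding before OMIs stop (Early OMIs group).
- 140 infants per arm (Sample size {14}).
- One session a day of 15 minutes (Early OMIs group).

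**Assumptions, not in the protocol**
- Gap g from first milk to the late start: 3, 5, 7 or 10 days.
- First-event rate λ: 0.03 per day, counted all day regardless of relation and equal in both arms; 0.01 and 0.05 as a range.
- Transition time runs from first milk.
- The comparison is of the share of infants with at least one event, tested two-sided at 5%.

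**Step 1: window lengths**
- Early: 11.36 + 2 = 13.36 days.
- Late: 13.40 + 2 − g = 15.40 − g days.
- Equal when 13.36 = 15.40 − g, so g = 2.04 days.

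An infant who takes milk while still on nasal CPAP has g of at least 2 days. About an hour of CPAP after first milk (0.04 day) is therefore enough to make the early window the longer one on average, even with the pilot's faster early arm.

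**Step 2: spurious difference**

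Share with an event = 1 − exp(−λ × window). Early arm at λ = 0.03: 1 − exp(−0.03 × 13.36) = 33.0%. The chance of significance is from a two-proportion z test with 140 per arm.

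| Gap g (days) | Late window (days) | Late share | Significant with no OMI effect |
|---|---|---|---|
| 3 | 12.40 | 31.1% | about 6% |
| 5 | 10.40 | 26.8% | about 21% |
| 7 | 8.40 | 22.3% | about 52% |
| 10 | 5.40 | 15.0% | about 95% |

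**Step 3: sensitivity at g = 7 days**
- λ = 0.01: about 23%. λ = 0.05: about 69%.
- Equal transition time of 13.40 days plus 48 h in both arms, λ = 0.03: 37.0% against 22.3%, about 77%.
- Events counted only during sessions, λ = 0.03: 15/1440 of each day is at risk, giving 0.42% against 0.26% of infants, or about 0.6 against 0.4 infants per arm (140 × 0.0042 and 140 × 0.0026). The artefact is then negligible.

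**Step 4: would a rate per patient-day cure it?**

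It removes the effect of window length but not that of respiratory status. Take g − 2 days on support inside the early window, none in the late window, and assume that the event rate doubles on support. The early-to-late ratio of daily rates is (2(g − 2) + 13.36 − (g − 2)) / 13.36. For g = 3, 5 and 7 this is 14.36/13.36 = 1.07, 16.36/13.36 = 1.22 and 18.36/13.36 = 1.37, again with no OMI effect.

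**The case against.** **Only study-related events count.** Read literally, a background desaturation is an adverse event in neither arm, and the artefact disappears. This is the strongest point, and it is why the figures above, which ignore relatedness, show what could happen rather than what will. It does not remove the asymmetry. Relatedness is hard to judge for desaturation or apnea in an infant on support. Before OMIs begin, a late-arm infant can hardly have an event attributed to them, whereas the same event in an early-arm infant can be.

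**The intervention period may mean the sessions.** Section {22} speaks of monitoring during the intervention, and a session lasts 15 minutes. On that reading background events barely accrue, as Step 3 shows. The phrase might also mean the hospital phase as opposed to follow-up, which would be nearly a common window. The protocol does not say which is meant.

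**The test is not fixed.** Section {20a} says "chi-square tests will be utilized for categorical variables" in general terms and does not tie that test to safety. A reader might infer that the plan compares the proportion of infants with any event; that is an assumption made here to show a size. A denominator may properly be left to an analysis plan. The difference in respiratory status would remain under a per-day rate.

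**The early window need not be longer.** Below a gap of 2.04 days, with the pilot means, it is not. The late window can also include high-flow time, since the Late OMIs group section names only nasal CPAP while the Table 2 footnote names non-invasive ventilation. Those two passages must be reconciled.

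**Conclusion.** The point stands as a should-fix for a secondary safety outcome. The counting window is tied to the randomised start time, so events between the two start points can enter from one arm only. The likely direction is against the early arm, and events that early OMIs prevent in that interval cannot be seen.

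The size cannot be derived from the protocol. The range of about 6% to 95% for gaps of 3 to 10 days rests on the assumed gap and event rate, all-day counting regardless of relation, and the pilot means.

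A reader might go further and infer that a false safety signal is all but certain, or that no safety finding could be interpreted. The documents support neither. Short gaps leave the error rate near its nominal level, session-based counting makes the artefact negligible, and related events at or near sessions while early-arm infants are on support remain informative about tolerance. The objectives in {7} name no safety hypothesis, and the primary comparison of transition time does not depend on this window.

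**What to change.** - Compare adverse events between arms over one common window, randomisation to discharge, by ITT, both per infant and per patient-day, regardless of judged relation to OMIs.
- Report events during or shortly after a session separately, as a descriptive rate per session. This keeps the tolerance information that the present wording seems to aim at.
- State in the Safety indicators section what the intervention period means and which denominator the rate uses.

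The cost is a change of wording and the extraction of late-arm events before OMIs start from existing records, which is extra transcription. Trial status describes recruitment as under way and section {21b} plans no interim analysis, so the change can be made without sight of outcomes by arm.
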